#### Adverse events

If serious injuries occur in the aerobic exercise group or the *Yi Jin Jing* group, such as a severe joint injury that makes it impossible to continue aerobic exercise or *Yi Jin Jing* intervention, it should be reported as an adverse event, and these subjects will stop aerobic exercise or *Yi Jin Jing* intervention and receive the usual medication, which is taking Diane-35. In case of adverse events, the study will have its own physical trainers and specialized practitioners to ensure proper measures are taken in cases of adverse events. Monitoring of adverse events for the aerobic exercise and *Yi Jin Jing* during the trial will include acute pain and heart rate. Therefore, adverse events occurring are estimated to be low.

Side effects of taking Diane-35 including headaches, nausea, weight gain, breast tenderness, and loss of libido will be monitored. If side effects occur, the drug should be stopped immediately for observation and the timing of continued use should be determined by the doctor. Serious adverse reactions will be reported to the ethical committee and other reactions that are thought to be causally associated with the intervention will be managed and recorded in the study.

If a subject suffers a sports injury, such as an ankle injury or muscle strain, during aerobic exercise or *Yi Jin Jing* training, the investigator will manage the acute phase of the sports injury according to the “PRICE” principle. PRICE stands for Protect, Rest, Ice, Compression, and Elevation. After the 48-h acute period, the investigator will provide the subject with appropriate free physiotherapy, such as muscle strength training and functional training. For the control subjects taking oral contraceptives, any side effects of the pill will be adjusted by the doctor and the cost of the examination and medication will be borne by the subject. Exercise and dietary advice and education will continue to be provided to all subjects after the 12-week study.

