#### Adherence and compliance

Prior to allocation, all participants will undergo a face-to-face education program with a doctor. All patients are assigned to smart phone app support. These steps are taken to ensure adherence. Control group patients will be asked to send monthly self-monitored information regarding their medication usage and any side effect via their phones for 3 months. Adherence and compliance will be determined from supervised exercise session attendance. Data from participants with less than 75% adherence will be included in the intention to treat analysis.

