## Blinding

Due to the characteristic of exercise intervention, all participants and the aerobic exercise supervisor and *Yi Jin Jing* instructor will not be blinded. But the staff who undertake outcome measuring and statistician who undertakes data processing will be blinded to group allocation.

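### Control women pay for follow-up of pill side effects while injured exercisers get free physiotherapy, which may weaken safety follow-up and retention in the comparator arm

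*Protocol article*

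**What the plan says.** The last paragraph of the Adverse events section of the protocol article sets a cost rule by arm.

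- **Exercise arms.** For a sports injury, "the investigator will manage the acute phase of the sports injury according to the “PRICE” principle". After 48 hours, "the investigator will provide the subject with appropriate free physiotherapy, such as muscle strength training and functional training".
- **Control arm.** The next sentence opens "For the control subjects taking oral contraceptives" and continues that "any side effects of the pill will be adjusted by the doctor and the cost of the examination and medication will be borne by the" participant.

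No other section reimburses the control arm.

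Three further statements bear on the point:

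- Adherence and compliance describes how information on the pill is collected: "Control group patients will be asked to send monthly self-monitored information regarding their medication usage and any side effect via their phones for 3 months".
- Adverse events gives the consequence of a side effect: "If side effects occur, the drug should be stopped immediately for observation and the timing of continued use should be determined by the doctor".
- Blinding states that "all participants and the aerobic exercise supervisor and *Yi Jin Jing* instructor will not be blinded".

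**The concern.** A woman harmed by her allocated treatment meets a different financial rule depending on her arm, and she knows which arm she is in. The charge falls where the trial depends most on what the participant chooses to disclose. Exercise sessions are led by a trainer or instructor, with acute pain and heart rate watched. Most of the listed pill effects (headache, nausea, tender breasts, reduced libido) are symptoms that the woman must mention.

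Three things are at stake:

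- **Safety.** A control woman with a mild or moderate symptom has a stated financial reason not to seek the follow-up that the protocol intends for her.
- **Completeness.** Side effects and pill stops may be recorded less fully in the comparator arm.
- **Retention.** Women with side effects may leave that arm, against which the Discussion hypothesises that both exercises lower AMH.

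**Working it through.** The point is about a rule, so the main check sets the statements side by side.

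| Question | Exercise arms | Control arm |
|---|---|---|
| Who handles the harm? | Investigator, then physiotherapy (Adverse events) | Doctor (Adverse events) |
| Who pays? | Physiotherapy is explicitly free; no charge is mentioned for acute care | Participant pays for examination and medication |
| How is harm noticed? | Supervised sessions; acute pain and heart rate monitored | Said to be monitored; the described route is the monthly phone report |
| How is adherence judged? | Attendance at supervised training | Self-reported medication use |
| Does she know her arm? | Yes | Yes |

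**Step 1: is the asymmetry stated?** Yes. It is written in adjacent sentences, and the charge is attached to the control arm by name. It is a fixed rule, not detail that a condensed article has left out.

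**Step 2: is there a route from the charge to the data?** Plausibly. Follow-up costs a control woman money, she is unblinded, and her own report is the main described source on both symptoms and pill use. A symptom or a pill stop that she does not mention could go unrecorded. Multiple imputation (Statistical methods) can condition only on what was recorded.

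**Step 3: can the effect be sized?** Not from the documents. They give no side-effect rate, no reporting rate and no arm-specific dropout. What can be shown is the scale of extra control losses, which are assumed here.

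- Inputs from Sample size: 30 per arm, about 20% attrition, AMH difference 13.2 pmol/L, SD 20.5 pmol/L, two-sided α = 0.05.
- Planned losses: 0.20 × 30 = 6 per arm, leaving 24. Each extra control loss adds 1/30 = 3.3 percentage points.
- Power for one exercise arm against control, by normal approximation: Φ(13.2 / (20.5 × √(1/24 + 1/n)) − 1.96), where n is the number of control women analysed.

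| Control n (assumed) | Control attrition | Power |
|---|---|---|
| 24 | 6/30 = 20% | 61% |
| 20 | 10/30 = 33% | 57% |
| 18 | 12/30 = 40% | 54% |
| 15 | 15/30 = 50% | 50% |

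For n = 24: 20.5 × √(2/24) = 5.92; 13.2/5.92 = 2.23; Φ(2.23 − 1.96) = 0.61. This starting value is below the protocol's 80% because 25 per group with these inputs gives 62% in a two-group comparison. That is a separate matter on which this point does not depend.

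The table shows lost precision only. It says nothing about the direction or size of any bias.

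**The case against.** The best case against has five parts.

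1. **Deterrence is inferred.** No section reports that cost deters anyone. This stands, so the effect can only be put as something that may happen.
2. **Reporting itself is free, and other routes may exist.** The phone report is requested from every control woman with no stated charge, and nothing makes a paid examination automatic once she reports. Side effects are said to be monitored, and weight gain would show in the before-and-after measurements. A reader might infer that pill effects become known only if a woman volunteers them and that volunteering them brings a bill. The text does not go that far. What remains is that any examination and medication that follow are charged to her.
3. **Exercise care is not shown to be free throughout.** Only physiotherapy after 48 hours is explicitly free; free acute care is implied. Who pays for a serious injury is not stated, nor who pays for side effects in an exerciser moved to Diane-35. This narrows the contrast without removing it.
4. **No planned harm comparison is distorted.** A reader might infer that a between-arm safety analysis is compromised. Outcome measurements lists no safety outcome and Statistical methods describes no harm test. The remaining concern is unequal capture of adverse events.
5. **AMH bias is not shown.** The protocol already stops the drug when a side effect occurs, so an unreported stop may change exposure little; what is lost is the record and the doctor's decision on continuing. Participants with low adherence stay in the intention-to-treat analysis. Biased dropout would also have to be related to AMH, and the documents give no such link.

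These parts limit the claim about bias. They do not answer the objection on fairness and safety follow-up.

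**Conclusion.** The point holds as a safety and fairness problem. The protocol charges women in one arm for follow-up of harm from their allocated treatment, while injured exercisers receive investigator-managed acute care and explicitly free physiotherapy. It also carries a plausible but unquantified risk of unequal adverse-event capture and retention in the comparator arm. That risk rests on three conditions found in the text (unblinded participants, mainly self-reported pill data, charged follow-up) and one assumption that is not in it: that cost affects what some women do. The solicited phone report works in the other direction.

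A reader might go further and conclude that the AMH comparison is biased. The documents do not support this: they give no rate of cost-driven silence or dropout and no link between such dropout and AMH. No planned analysis is invalidated. The change is still worth making because it is cheap and removes an incentive specific to one arm.

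**What to change.** Change the cost sentence in Adverse events so that the trial bears the cost of examining and managing suspected Diane-35 side effects in any participant taking the drug through the trial. Include exercisers who are moved to it after a serious injury, whose position is now unstated. Tell all participants this at the face-to-face education session held before allocation, and align the participant information. Leave the clinical handling of side effects as it is; only the question of who pays changes.

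The cost is a modest budget for outpatient visits and related medication in about 30 control women plus any switched exercisers, at the hospital that already performs the trial's tests. No new procedure or staff is needed. For women already enrolled, the change can apply from the date it is adopted.

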#### Adherence and compliance

Prior to allocation, all participants will undergo a face-to-face education program with a doctor. All patients are assigned to smart phone app support. These steps are taken to ensure adherence. Control group patients will be asked to send monthly self-monitored information regarding their medication usage and any side effect via their phones for 3 months. Adherence and compliance will be determined from supervised exercise session attendance. Data from participants with less than 75% adherence will be included in the intention to treat analysis.

#### Study measurements

Prior and post to intervention, the following will be measured. Transvaginal ultrasound scan will be performed during the early follicular phase (cycle days 3–5) to document ovary morphology, including antral follicle count and ovarian volume. Fasting blood will be taken for 2–5 days during spontaneous menstrual cycle to check biochemical profiles, including AMH, LH, FSH, T, E_2_, sex hormone binding globulin (SHBG), dehydroepiandrosterone sulfate (DHEA-S), fasting insulin (FINS), and fasting blood glucose (FBG) level. Free androgen index (FAI = T × 100/SHBG) and homeostasis model assessment of insulin resistance (HOMA-IR = FINS × FBG /22.5) will be calculated. All ultrasound and blood tests were performed at the medical laboratory of Yueyang Hospital. All participants will receive a menstrual diary to record menstrual bleedings, menstrual frequency which will be calculated by dividing the number of menstrual bleedings by 3 (ordinal variables: “0,” “1/3,” “2/3,” “1”). Anthropometric indicators including weight, height, and BMI will be measured.

#### Outcome measurements

The primary outcome is serum AMH level. AMH is the best marker of the ovarian function; it could be noticed as a suitable hormonal marker of the ovarian follicular count and as a diagnostic marker for ovarian hyperandrogenism [44–46]. Therefore, we choose AMH as the primary outcome.

Secondary outcomes include:(1). Menstrual frequency.(2). Biochemical profile including FSH, LH, T, E_2_, SHBG, DHEA-S, FAI.(3). Antral follicle count and ovarian volume.(4). BMI(5). HOMA-IR

#### Participant timeline

Participant timeline is described in Fig. 2.

**Fig. 2 Fig2:**
[figure not shown]
Participant timeline

#### Sample size

AMH is the target effect, according to a similar research by Moran [47], where the mean AMH level before intervention was 59.1pmoL/L, standard deviation was 20.5pmoL/L, and AMH declined by 13.2pmoL/L in response to exercise. We require 25 participants per group to achieve a power of 80%, two-sided *α* = 0.05. With an approximate attrition rate of 20%, we will recruit 90 participants in total with 30 participants per group.

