### Statistical methods

The intention-to-treat principle will be used in the statistical analysis. We will use multiple imputation, based on 5 replications and a chained equation approach method in the R MI procedure, to account for missing data. Continuous variables will be presented by mean ± standard deviation. We will use the Kolmogorov–Smirnov test to see the normality and Levene test to see homogeneity of variance. Data transformations, such as logarithmic transformation or arcsine square root transformation, will be applied in cases of a non-normal distribution. Analysis of variance (ANOVA) will be used for comparing the differences between groups, and Bonferroni test will be applied if the difference is found to be significant. Paired *t*-test will be used for comparing the differences within groups. Differences between groups of the categorical data (menstrual frequency) will be compared by Kruskal–Wallis test, and Nemenyi test will be applied if the difference is found to be significant. A two-sided *P* value less than 0.05 will be considered significant.

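### The 25 per group for 80% power does not follow from the printed AMH inputs for an unadjusted between-group comparison; on those inputs power is about 61%

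*Protocol article*

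**What the plan says.** All statements are in the protocol article.

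- Outcome measurements: "The primary outcome is serum AMH level".
- Sample size, inputs from a similar earlier study: "the mean AMH level before intervention was 59.1pmoL/L", "standard deviation was 20.5pmoL/L", and "AMH declined by 13.2pmoL/L in response to exercise".
- Sample size, conclusion: "We require 25 participants per group to achieve a power of 80" per cent, with "two-sided *α* = 0.05".
- Sample size, attrition: "With an approximate attrition rate of 20%, we will recruit 90 participants in total with 30 participants per group".
- Study design and Objectives: a superiority trial with three parallel arms allocated 1:1:1, whose main objective is to compare aerobic exercise with *Yi Jin Jing*. The Discussion adds the hypothesis that both lower AMH relative to the contraceptive control arm.
- Statistical methods: groups are compared by ANOVA with no baseline covariate named, and then "Bonferroni test will be applied if the difference is found to be significant". Changes within a group are tested by paired *t*-test.

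**The concern.** The section prints an effect, a standard deviation, an alpha, a power and a sample size, so the last can be checked against the others. For a comparison between arms they do not agree.

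The effect is also of a different kind from the one the trial tests. It is the fall in AMH after exercise, paired with the SD of AMH before the intervention. Using it as a difference between arms assumes that the comparator does not change. Here the comparator is either a drug arm or a second exercise arm that the authors also expect to lower AMH.

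The stake is how a null result would be read. If the trial is taken to have 80% power for 13.2 pmol/L, a non-significant result looks like good evidence against a difference of that size. With power near 60% it is much weaker evidence.

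**Working it through.** **Inputs.** Difference δ = 13.2 pmol/L, SD σ = 20.5 pmol/L, two-sided alpha 0.05, target power 80%, 25 per group, 30 recruited per group, 20% attrition (all from Sample size). Three arms, ANOVA and Bonferroni come from Study design and Statistical methods. Assumption for steps 1 to 3: 13.2 stands in for a between-arm difference, and the outcome is analysed without baseline adjustment.

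Standardised difference: 13.2 / 20.5 = 0.644.

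**1. Trying to reproduce 25 for two groups.** Normal approximation: n = 2(1.960 + 0.842)² / 0.644² ≈ 37.9, so 38 per group. The exact *t* calculation gives 39. Neither is 25. A one-sided 0.05 test would need about 30, and the section states two-sided.

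**2. Power at the planned size.** Noncentrality = 0.644 × √(n/2), with 2n − 2 degrees of freedom, exact noncentral *t*:

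| Evaluable per group | Noncentrality | Power, alpha 0.05 |
|---|---|---|
| 24 | 2.231 | 58.9% |
| 25 | 2.277 | 60.7% |
| 30 (no attrition) | 2.494 | 68.9% |
| 39 | 2.843 | 80.2% |

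Using the pooled ANOVA error (72 degrees of freedom) at 25 per group changes 60.7% only to 61.3%. The difference detectable with 80% power is 16.6 pmol/L at 25 per group and 16.9 pmol/L at 24.

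**3. The three-group ANOVA.** Noncentrality λ = n Σ(μᵢ − μ̄)² / σ².

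- Two means equal and the third 13.2 away: Σ = 116.16, so λ = 25 × 116.16 / 420.25 = 6.91. Power is 63%, and 80% needs 36 per group.
- Means evenly spaced over 13.2: Σ = 87.12, so λ = 25 × 87.12 / 420.25 = 5.18. Power is 50%, and 80% needs 48 per group.

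Pooling both exercise arms (50) against control (25) gives about 75%.

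**4. What would give 25.** Let r be the correlation between baseline and follow-up AMH, with SD 20.5 at both times.

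- Baseline-adjusted comparison, SD = 20.5√(1 − r²): 80% at 25 per group needs r of about 0.61.
- Comparison of change scores, SD = 20.5√(2(1 − r)): 80% at 25 per group needs r of about 0.68. At r = 0.5 this SD is again 20.5 and power is again 61%.
- Unadjusted comparison with a smaller SD: about 16.3 instead of 20.5.
- Paired test within one group: r of about 0.39 gives an SD of change of 20.5 × √1.22 = 22.6, and 25 women then give about 80%.

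The section prints none of these assumptions.

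**5. Secondary: Bonferroni follow-up pairs.** Three pairs give 0.05 / 3 = 0.0167. Power per pair for 13.2 pmol/L is 42.7% at 25 per group and 40.8% at 24. If only two pairs were tested (0.025), it would be 49% at 25.

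**6. Minor: attrition.** 30 × 0.8 = 24, one below the stated 25. Keeping 25 after 20% loss needs 25 / 0.8 = 31.25, so 32. The printed 30 equals 25 × 1.2.

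**The case against.** The strongest reply is that 25 may come from a calculation that the article does not spell out. The effect is a pre-post decline, the plan includes a paired *t*-test, and a paired calculation with r near 0.39 gives about 25. So it would be wrong to say that no paired calculation leads to 25. This is a plausible source, though unproven. It does not rescue the claim, because a paired test within one arm says nothing about superiority between arms.

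A second reply is that Statistical methods does not say whether ANOVA is applied to follow-up values or to changes, and Study design speaks of comparing post-test measurements with baseline. This stands in part. A reader might infer that 25 per group is too few for every between-group analysis of AMH. The documents do not support that: with change scores or baseline adjustment and a high enough correlation, 25 suffices at alpha 0.05. The shortfall belongs to the unadjusted comparison on the printed inputs.

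A reader might also take the 43% for Bonferroni pairs as the headline. Sample size claims power at alpha 0.05 only, and Bonferroni enters as a follow-up to a significant ANOVA, so no stated power claim is broken at 0.0167. That figure is background.

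On attrition, 20% is given as approximate, 30 per group keeps 25 at a loss of 16.7% (5 / 30), and multiple imputation is planned. One woman per group moves power from 60.7% to 58.9%. The slip is real but small.

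Finally, a condensed article may leave the test and the correlation to the full protocol. Their absence is not the point here. The point is that the printed inputs do not yield the printed sample size for the stated objective.

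**Conclusion.** The point holds for an unadjusted comparison between arms. On the printed inputs, 80% power at two-sided 0.05 needs 39 evaluable women per group, not 25. With 25 the power is about 61%, with 24 about 59%, and the three-group ANOVA has about 50% to 63% at 25, depending on the pattern of means.

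These figures rest on treating the 13.2 pmol/L decline as a difference between arms, on SD 20.5 for the analysed variable, and on no gain from baseline. A reader might take 61% as the trial's actual power. The documents do not establish that, since they give no between-arm difference and no correlation. The first assumption favours the plan if the comparator arm also lowers AMH; the third works against the plan if the correlation is high and the analysis uses it.

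**What to change.** Keep 90 patients and choose one of two edits.

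1. **Restate Sample size only.** Say that 13.2 pmol/L was a within-group change after exercise. State that, with 24 evaluable per group after 20% attrition, the trial has about 59% power for a between-group difference of 13.2 pmol/L (SD 20.5, unadjusted, two-sided 0.05) and 80% power for 16.9 pmol/L.
2. **Change the AMH analysis as well.** Name a baseline-adjusted ANCOVA for AMH in Statistical methods, and give the power in Sample size under explicit assumed correlations. With 24 per group and a difference of 13.2 pmol/L it is about 71%, 78% and 86% for correlations of 0.5, 0.6 and 0.7. Both sections must change together, because Statistical methods now names ANOVA without a covariate.

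In either case, correct the evaluable number to 24 per group. The cost is an edit to one section, or two if ANCOVA is chosen. Under the first option the stated power is clearly less favourable; under the second it depends on the assumed correlation. No extra patients are needed.

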#### Recruitment

Enough patients will be recruited through posters, word of mouth, and recommendations from gynecologists.

#### Randomization and concealment

Eligible participants will be randomly assigned into the control group or the intervention group (aerobic exercise group or *Yi Jin Jing* group) with an allocation rate of 1:1:1. The randomization procedure will be conducted by an independent statistician using a computerized program. The allocation sequence will be stored in a sealed envelope and will not be announced until the baseline measurements have been completed.

